***Fidelity***		
Supervised exercise	Number of supervised exercise sessions (individual or group) attended with reasons for non-attendance where applicable. Supervised exercise intensity and progression (i.e., changes in the supervised exercise level).	Reported by the physiotherapists in the digital clinic after each supervised exercise session. The Borg RPE scale will be used to assess exercise intensity.
Prescribed exercise	Number of study participants who have been prescribed exercises and prescribed exercise dose (i.e., number of exercises and repetitions).	Information registered automatically in the digital clinic at point of prescription by the physiotherapist.
Behaviour change techniques	Number of study participants taking part in individual counselling and structured follow-ups. Number of goals, goal characteristics, and goal fulfilment across the intervention period.	Recorded by the physiotherapist in the digital clinic after each individual counselling and follow-up session.
Technology usage	Number of times the STAAR app is accessed by study participant and the purpose of accessing (e.g., exercise programme, educational videos and self-monitoring). Number of technical problems including inability to connect to the STAAR app or attending meeting with physiotherapist.	STAAR app access recorded automatically in the digital clinic. Technical problems reported by both participants and physiotherapists to the research team.

### Acceptability

Acceptability of the mHealth version of the i-REBOUND programme will be evaluated using the Telehealth Usability Questionnaire administered immediately post intervention via the STAAR app [45]. Further, a subset of study participants (*n* = 10–15) from the experimental group will be invited to two semi-structured individual interviews early (months 2–3) and late (months 5–6) during the programme for exploration of experiences regarding the mobile app in terms of usability and support, and the physical exercise and behaviour change components of the intervention. Data collection via two separate interviews will enable exploration of similarities and differences in participants’ perceptions and acceptability of mHealth at the different time points. To gain insight into experiences of intervention delivery, interviews will be conducted post-intervention with the physiotherapists responsible for delivering the interventions (*n* = 2–4). All interviews will be conducted via Zoom, audio and video-recorded and transcribed verbatim.

### Clinical outcomes

Clinical outcomes on the preliminary effects of the intervention will be collected at baseline and at 3, 6 and 12 months after the baseline assessments (Table 4). Study participants adherence to the measurement protocol will be monitored by the research team throughout the intervention period with reminders sent to participants through the STAAR app, as required.

**Table 4 Tab4:** Overview of clinical outcome measures for both experiment and control groups from baseline to one year follow up

Outcome measure	Data collection instrument	Baseline	Month 3	Month 6	Month 12
Physical activity	ActivPal accelerometer	✓	✓	✓	✓
Blood pressure	Omron M7 Intelli IT-AFIB blood pressure monitor	✓	✓	✓	✓
Self-efficacy for exercise	Exercise Self-Efficacy Scale	✓	✓	✓	✓
Balance confidence	Activities-Specific Balance Confidence scale	✓	✓	✓	✓
Walking ability	Generic Walk-12 Scale	✓	✓	✓	✓
Fatigue	Fatigue Severity Scale	✓	✓	✓	✓
Psychosocial wellbeing	Depression Anxiety Stress Scale	✓		✓	✓
Health related quality of life	EuroQol-5 Dimensions	✓		✓	✓

*Physical activity* (steps per day and time spent sedentary, upright, and walking) will be measured using activPAL activity monitors [46]. Monitors will be posted to participants at each assessment point with a pre-paid return envelope. The participants will be asked to wear the device on their non-hemiparetic leg (or dominant leg if no hemiparesis) for 7 consecutive days, after which they will return the device to the research team.

*Systolic and diastolic blood pressure* will be measured using an automated blood pressure monitor (Omron M7 Intelli IT-AFIB) [47] sent to participants prior to baseline measurements. Participants will be instructed to take two recordings of blood pressure on the left upper-arm or the non-affected arm, twice a day (morning and evening) on 7 consecutive days [48] and record their results in the STAAR app. Recorded systolic and diastolic average values will be used for analysis where a minimum of 6 measurements or 3 days have been recorded. We will primarily focus on the evaluation of systolic blood pressure in this study due to the strong linear relationship between systolic blood pressure reduction and risk reduction of recurrent stroke [49].

Digital questionnaires administrated through the STAAR app will be used to assess self-efficacy for exercise, balance confidence, walking ability, fatigue, psychosocial wellbeing, and health related quality of life (see Table 4). The 9-item *Exercise Self-Efficacy Scale* will be used to assess the impact of factors such as weather, mood, and pain on the ability to continue exercising on a three times-per-week basis at moderate intensities for 20 min per session [50]. For each item, participants indicate their confidence to execute the behaviour on a 100-point percentage scale comprised of 10-point increments, ranging from 0% (not at all confident) to 100% (highly confident). Confidence in maintaining balance whilst performing daily activities will be assessed using the *Activities-Specific Balance Confidence scale* which has been specifically developed for use in stroke rehabilitation [51]. This 16-item tool considers various movements (e.g., walking, bending over) in a variety of physical environments (e.g., icy pavements, stairs) and the confidence performing these activities is reported on an 11-point ordinal scale ranging from 0% (“no confidence”) to 100% (“completely confident”). For the Exercise Self-Efficacy Scale and Activities-Specific Balance Confidence scale an average score is calculated (i.e., maximum 100%) and used for analysis. The Swedish version of *Generic Walk-12 Scale,* developed for use specifically for those with neurological conditions will be used to measure self-perceived walking limitations in everyday life during the past two weeks [52]. The first three items of the scale have three response categories (scored 0–2) whereas the remaining nine items have five response categories (scored 0–4). Item scores are summed to a total score with a possible range between 0 and 42 (higher score = more walking difficulties). The 9-item *Fatigue Severity Scale* will be used to evaluate the effects of fatigue on physical everyday activities and life [53]; a nine-item questionnaire with each item scored on a 7-point Likert scale ranging from 1 (‘‘disagree’’) to 7 (‘‘fully agree’’). The mean score of the nine items is presented as a fatigue score. The 21-item *Depression Anxiety Stress Scale* will be used to measure emotional states of depression, anxiety and stress [54]. Each of the three depression and anxiety scales contains 7 items whereby participants rate the extent to which they have experienced symptoms related to depression (e.g., hopelessness, lack of interest and involvement), anxiety (e.g., autonomic arousal, skeletal muscle effects) and stress (e.g., difficulty relaxing, being easily upset, irritable and impatient) over the past week using a 4-point Likert scale. Scores for depression, anxiety and stress are calculated by summing the scores for the relevant items. Health related quality of life will be measured using the *EuroQol-5 Dimensions questionnaire* including five items of different health domains; mobility, self-care, activities of daily living, pain and anxiety/depression, which is scored on 5-point Likert scale (“no problems” to “extreme problems”) and a visual analogue scale (0–100) where the endpoints are labelled “The best health you can imagine” and “The worst health you can imagine” [55].

## Analysis

Baseline characteristics will be presented in numbers and percentages, and in mean and standard deviation or median and interquartile range, depending on the normality of data distributions determined by visual inspection of plots and Shapiro–Wilk tests. Outcomes regarding feasibility (i.e., reach, adherence, safety and fidelity) and acceptability (i.e., Telehealth Usability Questionnaire) will primarily be analysed using descriptive statistics.

For the qualitative analysis of end users’ experiences of the i-REBOUND programme, interview transcripts will be analysed according to thematic analysis [56] following a six-phase dynamic process of data familiarisation, generating semantic and latent codes, actively developing initial themes, reviewing themes, defining and naming themes and producing the report. Inductive analysis will be carried out keeping the themes strongly linked to the data produced during interviews.

Preliminary effects of the mHealth version of the i-REBOUND programme will be analysed using an intention-to-treat and a mixed-effects model to analyse differences in clinical outcomes between the two groups (2 levels: experimental vs control) and over time (4 levels: baseline, and the 3, 6 and 12-months follow-up). Outcomes not meeting the assumptions for analysis using a mixed-effects model will be analysed using non-parametric tests.

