**Methods:**

One hundred and twenty participants with stroke or TIA will be recruited via advertisement. A parallel-group feasibility randomised controlled trial design with a 1:1 allocation ratio to 1) i-REBOUND programme receiving physical exercise and support for sustained engagement in physical activity through behavioural change techniques, or 2) behavioural change techniques for physical activity. Both interventions will proceed for six months and be delivered digitally through a mobile app. The feasibility outcomes (i.e., reach, adherence, safety and fidelity) will be monitored throughout the study. Acceptability will be assessed using the Telehealth Usability Questionnaire and further explored through qualitative interviews with a subset of both study participants and the physiotherapists delivering the intervention. Clinical outcomes on preliminary effects of the intervention will include blood pressure, engagement in physical activity, self-perceived exercise self-efficacy, fatigue, depression, anxiety, stress and health-related quality of life and will be measured at baseline and at 3, 6 and 12 months after the baseline assessments.

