### Participants

One hundred and twenty adults diagnosed with a stroke or TIA will be recruited across rural and urban areas of Sweden through advertisements at outpatient clinics, the Karolinska Institutet homepage, patient organisations and social media. The inclusion of 120 study participants builds on our aim to test the feasibility of the mHealth version of the i-REBOUND programme among people post stroke or TIA situated both in urban and rural areas, with variation in disability, exercise habits, physical activity levels, age, gender and technology use. The sample size is in line with recommendations regarding feasibility studies [36].

Inclusion criterion are: (i) between 3 months and 10 years post stroke or TIA at point of study enrolment, (ii) living at home, (iii) with the ability to walk short distances indoors with or without a walking device, (iv) able to use a smartphone, (v) have access to a stable internet connection, and (vi) ability to digitally self-identify using BankID. BankID is a Swedish smartphone and computer application considered to be secure and used by authorities to log into e-services and sign contracts electronically.

Exclusion criterion are: (i) already meeting the recommended physical activity levels of at least 150 min per week of moderate physical activity or at least 75 min per week of vigorous intensity physical activity [37] assessed using the International Physical Activity Questionnaire [38], (ii) severe health conditions (e.g. cardiac conditions, other neurological diseases and severe arthritis), (iii) significant cognitive impairment, neglect or aphasia compromising engagement in the intervention, or iv) enrolled in a concomitant clinical trial or participating in rehabilitation (e.g. aerobic exercises) at the time point of recruitment.

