### Randomisation

Following screening and baseline assessment, eligible participants will be randomised to either 1) an experimental group receiving the i-REBOUND programme or 2) a control group receiving the standard approach for physical activity promotion used in Sweden known as ‘Physical Activity on Prescription’ [16]. The randomisation will be performed in blocks of 2 and will be stratified according to mobility status (with/without walking aid) and geographical region (urban/rural areas). The randomisation schedule will be prepared by an independent researcher, and coded into a trial database, ensuring allocation concealment. The researcher responsible for data management and analysis will be blinded to group allocation.

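### The effect model makes the pre-randomisation baseline an outcome level without fixing equal baseline means or the treatment contrast, so precision can be lost needlessly

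*Protocol article*

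**What the plan says.** The Analysis section of the protocol article specifies, on an intention-to-treat basis, "a mixed-effects model to analyse differences in clinical outcomes between the two groups (2 levels: experimental vs control) and over time (4 levels: baseline", continuing with "and the 3, 6 and 12-months follow-up". Baseline is thus one of four levels of the time factor. The section names no group-by-time interaction, no constraint on the baseline means, no contrast or visit that carries the effect, and no covariates.

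The Randomisation section fixes the order of events: "Following screening and baseline assessment, eligible participants will be randomised". It also says that allocation is "stratified according to mobility status (with/without walking aid) and geographical region (urban/rural areas").

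Table 4 (Clinical outcomes) has assessments at baseline and months 3, 6 and 12 for most measures. For the Depression Anxiety Stress Scale and EuroQol-5 Dimensions the month 3 cell is empty, so those two have three time levels. The Analysis section states four levels without exception.

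The fourth study objective calls the effects preliminary and sets out to explore them. The size of 120 rests on feasibility, not power: "The sample size is in line with recommendations regarding feasibility studies".

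**The concern.** A measurement taken before allocation cannot respond to treatment, and randomisation makes its expected value the same in both arms. A model that treats it as an ordinary outcome level, with its own mean in each arm, does not use that fact. The treatment contrast at a follow-up visit then becomes the difference between arms in change from baseline. That is valid, but less precise than an estimate that conditions on baseline.

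Because the text does not say which term is the treatment effect, it also leaves open a group term pooled over all four visits, in which a visit with zero effect is averaged in.

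At stake are the preliminary effect estimates and their confidence intervals, part of the results that are to inform a full-scale trial.

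**Working it through.** The article gives no power calculation, standard deviation or correlation for these outcomes, so there is no stated figure to reproduce.

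**Inputs.** From the article: 120 participants and 1:1 allocation, so 60 per arm; four time levels (Analysis); three for two questionnaires (Table 4); baseline before randomisation. Assumed: equal variance (set to 1) at baseline and follow-up, correlation r between them of 0.5 to 0.7, no dropout.

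**1. Group-by-time contrast with free baseline means, at one visit.** Per-person variance of the change is 2(1−r). With adjustment for baseline, or a common baseline mean, it is 1−r². The ratio is 2(1−r)/(1−r²) = 2/(1+r). The 95% CI half-width is 1.96 × √(2 × variance/60), in SD units.

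| r | 2(1−r) | 1−r² | Variance ratio | SE ratio | Half-width, change | Half-width, adjusted |
|---|---|---|---|---|---|---|
| 0.5 | 1.00 | 0.75 | 1.33 | 1.15 | 0.36 | 0.31 |
| 0.6 | 0.80 | 0.64 | 1.25 | 1.12 | 0.32 | 0.29 |
| 0.7 | 0.60 | 0.51 | 1.18 | 1.08 | 0.28 | 0.26 |

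Both estimates are unbiased. The loss falls as r rises: at r = 0.8 the variance ratio is 2/1.8 = 1.11.

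**2. Group main effect pooled over all visits.** For a constant effect d after baseline and zero at baseline, equal weighting gives (0 + d + d + d)/4 = 0.75d. For the two questionnaires without month 3 it gives (0 + d + d)/3 = 0.67d. This applies only if that term is what is reported.

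**3. Stratification factors.** Assume that they explain a share R² of 0.1 to 0.2 of outcome variance, with the same effect at every visit.

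- Change contrast: with complete data, strata effects that are constant over time cancel within person. The variance is 2(1−r) with or without strata, so nothing is lost.
- Baseline-adjusted estimate: the variance is 1−r² without strata and (1−R²)(1−r′²) with them, where r′ = (r−R²)/(1−R²). At R² = 0.1 and r = 0.5, r′ = 0.444 and the ratio is 0.75/0.722 = 1.038, so the SE is 1.9% wider; at r = 0.7 the ratio is 0.51/0.50 = 1.02, or 1.0% wider. At R² = 0.2 and r = 0.5, r′ = 0.375 and the ratio is 0.75/0.6875 = 1.091, or 4.4% wider; at r = 0.7 it is 0.51/0.4875 = 1.046, or 2.3% wider.

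The strata are therefore worth about 1–4% in SE after baseline adjustment. In a linear model, leaving them out does not shift the estimate.

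**The case against.** The strongest defence is that baseline as one of four time levels is a standard longitudinal layout. A model constrained to a common baseline mean uses exactly those four levels, so the sentence is compatible with a good analysis. What separates the better fit from the poorer one is detail that a condensed article commonly leaves to a full protocol or analysis plan, and neither is shown. The analysis is also exploratory, and no stated decision depends on the width of these intervals.

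Much of this stands. The layout is not an error, and the weight must be low. It does not remove the point: the article does set out the factors and their levels, the usual fit of that wording has free baseline means, and a better specification is available with data already collected. The fixed four levels also disagree with Table 4 for two instruments, which needs correcting in any case.

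A reader might infer two stronger claims. One is that the planned model dilutes the treatment effect. The article never says that the pooled group term is the effect estimate; it speaks of differences between groups and over time, and under a group-by-time contrast there is no dilution. The other is that the stratification factors have been left out. The Analysis section lists no covariates and excludes none, so silence is not a decision to omit them.

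**Conclusion.** The point holds as an avoidable loss of precision and an undefined treatment contrast. It is not a demonstrated bias. Under the usual group-by-time fit with free baseline means, the variance at one visit is 18 to 33% larger than it need be, about 8 to 15% on the SE, if r lies between 0.5 and 0.7. These figures rest on equal variances over time, complete data and an assumed r; the article gives none of them. Shrinkage to 0.75d, or 0.67d for the Depression Anxiety Stress Scale and EuroQol-5 Dimensions, is conditional on reporting the pooled group effect. Including the strata is a small gain and corrects no bias. For an exploratory analysis in a feasibility trial this is a free improvement of modest weight.

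**What to change.** Reword the effect analysis as follows.

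- Define the treatment effect as the between-group difference at each follow-up visit, with a 95% CI.
- Fit group-by-visit terms at post-baseline visits only. Either keep baseline in the outcome vector with one common mean for both arms, or take it out of the time factor and enter it as a covariate.
- Match the time levels to Table 4: baseline and months 3, 6 and 12 in general, and baseline and months 6 and 12 for the Depression Anxiety Stress Scale and EuroQol-5 Dimensions.
- Include mobility status and region as fixed effects, or confirm that they are already included.

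The cost is a few sentences. All the variables are already collected, and neither the sample size nor the visit schedule changes.

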## Ethics and dissemination

Collected data will be treated confidentially and only the researchers will have access to the code key. Storage of personal information and registration of databases will follow General Data Protection Regulation laws. Sensitive paper files will be kept in a locked cabinet at the university or digitally on a secured server.

We recognise that people post stroke or TIA may experience cognitive and/or physical impairments, and thereby might have frail health and limited autonomy, potentially posing challenges during study participation. Furthermore, participants may share experiences regarding their disability or life situation which could be distressing for them. The research team and intervention physiotherapists are professionals with competence in how to meet and support people in such situations and in the case that professional help is required information and support for such contacts will be provided. We recognise participants may be disappointed with allocation to the control group, in which case they will be contacted by a member of the research team to discuss further.

Dissemination of study results is planned nationally and internationally via publication of scientific articles and through both poster and oral presentations at conferences.

## Discussion

Our study is a feasibility randomised controlled trial that aims to test the feasibility, acceptability and preliminary effects of the mHealth version of the i-REBOUND programme for promotion of physical activity in people post stroke or TIA across Sweden. This study has the potential to provide new insight and knowledge into the feasibility and acceptance of mHealth for promoting physical activity post stroke or TIA.

Although mHealth holds great potential to improve the accessibility of rehabilitation and health promotion services for people post stroke or TIA [30], several potential operational issues are involved in undertaking a completely digital intervention (i.e., without physical visits). Firstly, relying on technology is prone to technical problems, e.g., due to need for system updates and maintenance, and difficulties managing technology among study participants. Regarding the latter, people post stroke might have cognitive, visual and fine motor impairments affecting their ability to manage technology, e.g., difficulties with reading the font on a screen, orienting the user-interfaces and manual handling of the device [57, 58]. To minimise these risks and facilitate the intervention's reach, the intervention will be delivered using a mobile app developed together with people post stroke or TIA and physiotherapists to foster usability and to meet the needs of people post stroke/TIA [34]. Written and digital information on usability for study participants and physiotherapists delivering the intervention have also been established, as well as routines regarding how to support study participants when technical problems occur. Furthermore, younger age, high level of education and good health status have been associated with greater uptake of new technology for remote services among older adults during the pandemic [59]. This combined with recruitment through advertisement leads to a risk that the present intervention mainly reaches a certain sub-group of people post stroke or TIA. The evaluation of reach and uptake of this intervention is therefore vital for programme feasibility.

This trial investigates a complex mHealth programme with multiple interacting intervention components across a 6-month period. Conducting a large-scale feasibility randomised controlled trial, with an embedded qualitative study, is an important step to capture key uncertainties and understand what needs to be developed or adapted before commencing the full scale randomised controlled trial. Assessment of feasibility and acceptability of the intervention in a Swedish setting is also deemed necessary since the intervention has been developed in Australia [32, 60]. Physiotherapists will be trained in applying the mHealth version of i-REBOUND programme to optimise standardisation, promote adherence to the multifaceted content and ensure optimal quality of intervention delivery. It is also important to consider aspects of the study design (e.g., recruitment, drop-outs and assessment protocol) and safety and fidelity of key intervention components (i.e., physical exercise and behavioural change strategies) which are successfully delivered and which parts of the intervention that are potentially compromised. The transparent reporting should be of benefit to others who wish to replicate the feasibility evaluation of mHealth intervention for the promotion of physical activity post stroke or TIA, whilst avoiding repetition of disadvantageous elements.

